## Abstract

**Background::**

Food insecurity affects up to 30 % of pregnancies and is associated with worse maternal and infant health. Healthcare systems are implementing interventions to assist patients with food insecurity, but rather than providing a single intervention, adaptively providing interventions could be a more effective strategy. The objective of this study is to determine the feasibility of adaptively providing interventions to assist pregnant patients who report being food-insecure.

**Methods/design::**

We will conduct a pilot sequential multiple assignment randomized trial at obstetrics clinics from one health system. Adults (*N* = 60) who are pregnant and food-insecure will be randomized at their initial prenatal visit to one of two first-stage interventions for 3 months: 1) electronic health record (EHR) referral to WIC or 2) EHR-referral to WIC + care navigation. Participants who do not have ≥2-point improvement in food insecurity after 3 months will be re-randomized to one of two second-stage interventions for an additional 3 months: weekly delivery of 1) produce or 2) medically-tailored meals. In Aim 1, we will determine the feasibility of recruitment, and in Aim 2, we will evaluate the feasibility of re-randomization, retention, and data collection. In Aim 3, we will advance our understanding of how, why, and under what circumstances participants achieved improvements through semi-structured interviews.

**Conclusions::**

This will be the first study to test an adaptive intervention to assist pregnant patients with food insecurity and will inform a future fully-powered trial. Given the growing interest among health systems, an efficacious, adaptive food insecurity intervention could be broadly disseminated.

**Trial registration::**

The study was registered with ClinicalTrials.gov (NCT06942598) on April 23, 2025.

## Background

1.

The U.S. is facing a maternal and infant health crisis with approximately 700 maternal deaths and 50,000 life-threatening pregnancy events occurring each year [1–3]. Maternal deaths in the U.S. are now less likely to be due to direct complications of childbirth and are increasingly due to endocrine (e.g., gestational diabetes mellitus) or cardiovascular (e.g., pre-eclampsia) conditions directly related to nutrition-related chronic diseases [4,5]. One significant contributor to maternal morbidity and mortality is food insecurity (FI), or the lack of consistent access to the food needed for a healthy life [6,7]. In 2023, 13.5 % of U.S. households were food insecure, and up to 30 % of pregnancies are impacted by FI [8,9]. FI has been associated with inadequate or excessive gestational weight gain, gestational diabetes mellitus, and pregnancy-induced hypertension as well as increased risk of preterm birth and infants being born low birth weight [9–13].

To mitigate the impact of FI on health, national healthcare organizations, such as The American College of Obstetricians and Gynecologists, have recommended that health systems address FI as a routine part of clinical care [14–16]. The integration of interventions to address FI in clinical care settings has been termed “Food is Medicine” [17–19]. Three Food is Medicine interventions that are being used include: 1) referring patients to government benefits intended to support nutrition (e.g., the Special Supplemental Nutrition Program for Women, Infants, and Children (WIC)) or directly providing food through the use of 2) produce prescriptions (Produce Rx) and 3) medically-tailored meals (MTM) [19–21].

Despite the growing use of Food is Medicine interventions, research on the impact of healthcare system-based interventions to reduce FI in pregnancy remains limited [22,23]. Additionally, studies have found variability in the success of any one FI intervention [24,25]. For example, studies referring patients to government programs found only 30–40 % of patients received new benefits [26,27]. Although, Produce Rx and MTM may be more effective than referrals alone, they are costlier and more resource intensive, which could limit broad dissemination and scalability [24,25].

Rather than offer a single intervention, adaptively providing Food is Medicine interventions could provide a more equitable and efficient approach to assist pregnant patients. Adaptive, or stepped-cared, interventions provide a lower resource intensive intervention first, and then a higher resource intensive intervention to those more in need or who do not respond to the initial intervention [28–30]. However, there have been no adaptive health-system integrated interventions tested to assist pregnant patients with FI. To address this gap in the literature, we will conduct a pilot sequential multiple assignment randomized trial (SMART) to test the feasibility of adaptively providing Food is Medicine interventions to pregnant patients.

## Methods

2.

### Ethics statement

2.1.

The Wake Forest University School of Medicine Institutional Review Board (IRB) has reviewed and approved all the procedures outlined in this protocol. The study was prospectively registered with ClinicalTrials.gov (NCT06942598) prior to recruitment of the first participant. We have also included an independent safety officer who will review participant data to assess for any adverse events.

### Study setting

2.2.

This study will include patients from Atrium Health Wake Forest Baptist (AHWFB). AHWFB is a clinically-integrated, academic medical center comprised of the Atrium Health Wake Forest Baptist Medical Center, the Wake Forest University School of Medicine, and outlying affiliated hospitals and physician practices. AHWFB serves patients at over 350 care locations. We will conduct this study at obstetrics clinics affiliated with AHWFB.

### Overall study design

2.3.

Guided by the impact of FI on health and Food is Medicine conceptual frameworks [17,31–33], the objectives of the “Feasibility of an ADAPTive intervention to improve food security and Maternal-Child Health (ADAPT-MCH)” are to: 1) determine the feasibility of recruitment and retention and 2) generate preliminary estimates of the potential effectiveness of the interventions in anticipation of a large, definitive SMART to improve FI. A fully-powered SMART is needed to answer two questions: 1) as WIC is an evidence-based program shown to reduce FI and improve pregnancy outcomes, is a direct electronic health record (EHR) referral to WIC enough to reduce FI or do pregnant patients not already enrolled in WIC need a referral plus assistance from a care navigator? 2) for people who do not have an improvement in FI from the initial intervention, should healthcare settings provide Produce Rx or MTM? This pilot study is necessary to determine the feasibility of recruitment, re-randomization, retention, data collection, and adaptively providing FI interventions [34]. Data from this study will provide information to refine the study protocol and estimate measures of variance to assist in sample size calculations to inform a future fully-powered SMART.

The proposed pilot study is a single site two-stage SMART (Fig. 1). We will enroll 60 patients who are pregnant and food-insecure from obstetrics clinics affiliated with AHWFB. Using a computer-generated randomization table to ensure allocation concealment, eligible consenting participants will be equally randomized using permuted blocks of size 2,4, or 6 (1:1) to 1 of 2 first-stage interventions: 1) EHR referral to WIC or 2) EHR referral to WIC + care navigation. We will re-assess all participants at 3 months. Participants who do not have ≥2-point decrease in FI based on the 10-item adult USDA Food Security Survey Module (FSSM) (suboptimal improvement, i.e., non-responders) will be equally re-randomized using permuted blocks of size 2, 4, or 6 to 1 of 2 second-stage interventions: 1) Produce Rx or 2) MTM [7]. The USDA FSSM with a 30-day look back period measures food security over the prior 30 days. We will use the standardized scoring provided by the USDA, which produces a raw score from 0 to 10 with higher scores indicating worse FI. Due to the nature of the intervention, neither study staff nor participants are blinded to their assigned group.

In Aim 1, we will determine the feasibility of recruitment and which first-stage intervention is potentially more effective in reducing FI. In Aim 2, we will evaluate the feasibility of re-randomization, data collection, and retention and compare preliminary estimates of change in FI of providing Produce Rx versus MTM among participants who did not respond to the first-stage intervention. In Aim 3, we will advance our understanding of how, why, and under what circumstances participants achieved improvements to the interventions. Participants will engage in the interventions for up to 6 months, and we will follow all participants to after they have delivered. A 6-month intervention period was selected in keeping with similar FI studies [22,23]. As secondary outcomes, we will evaluate maternal and infant outcomes (Table 2) including the number of participants who are diagnosed with gestational diabetes, have excess gestational weight gain, pre-eclampsia, infant birth weight, and pre/post-term delivery based on data extraction from the EHR. Based on the impact of FI on health conceptual framework, we will also assess changes in nutritional, psychological, and compensatory pathways from baseline to 6 months [31–33]. As an exploratory aim, participants will wear a continuous glucose monitor (CGM) at 2 time points: baseline (first 2 weeks) and at 6-month follow up.

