### Recruitment and consent

2.4.

As part of routine care at the participating obstetrics clinics, any patient who believes they may be pregnant undergoes a pregnancy test and an ultrasound for confirmation of pregnancy followed by a nurse intake visit if a viable pregnancy is identified. The nurse intake visit is ideally performed at 8 weeks gestation. Patients then return 1–2 weeks later to meet the obstetrician or advance practice provider for an initial prenatal visit and begin prenatal care. During the initial 8-week nurse visit, all patients are screened for FI using the validated 2-item Hunger Vital Sign^™^ [35]. The measure asks: 1) “Within the past 12 months you were worried that your food would run out before you got money to buy more”, and 2) “Within the past 12 months the food you bought just didn’t last and you didn’t have money to get more.” Participants who respond “Often true” or “Sometimes true” to either question are considered food insecure, and responses to the items are captured as structured data elements in the electronic health record (EHR). Compared to the USDA FSSM (gold standard for assessing food security) [7], this 2-item measure has high sensitivity (97 %) and good specificity (83 %) and has been used in numerous prior studies in clinical settings [35–38]. Given this is a pilot study with a small sample size and to allow the interventions time to take effect, we will only include patients who are presenting in their first trimester (exclude patients presenting for the initial nurse visit in their 2nd or 3rd trimester). Using structured EHR data and a recurring weekly query, our research team will call all patients who are potentially eligible prior to their initial visit with the obstetrician/midwife to introduce them to the study and determine interest in participating. Potentially eligible and interested patients will be approached in the clinic at the time of their visit to assess eligibility, discuss study procedures, obtain consent, and collect baseline data. Patients will be eligible if they meet the prespecified inclusion and exclusion criteria (Table 1). After baseline data are obtained, participants will be randomized. We will continue this process until we reach our target sample size of 60 (see Power and Sample Size).

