#### Stage 2 interventions

2.5.3.

Produce Rx: Participants randomized to this arm will receive $10 worth of fruits and vegetables each week from our community partner, Help Our People Eat (H.O.P.E.) of Winston Salem. H.O.P.E. is a non-profit that distributes nutritious meals and fruits and vegetables to neighborhoods throughout Forsyth County to help families with FI. H.O.P.E. also collaborates with local farmers to provide a Neighborhood Produce Market that provides low-cost produce. Through H.O.P.E’s prior work, $10 of produce provides enough fruits and vegetables for a family of 4 for 2–3 days. Weekly deliveries of produce will be made to a participant’s home for 3 months, include a mix of fruits and vegetables depending on the season, and provided by local farmers.MTM: MTM will be provided by our community partner, Providence Kitchen, a program of Second Harvest Food Bank of Northwest NC. Participants will receive 10 medically-tailored refrigerated or frozen meals (5 lunches and 5 dinners) delivered to their home weekly for 3 months. All meals are planned by a registered dietician and tailored to meet the nutritional needs of pregnant women. Meals will require minimal preparation time, and will be packaged such that they can be re-heated by stove, oven, or microwave. Participants will be asked not to share the meals with family members. Consumption of meals and food sharing with other household members will be measured using food consumption diaries.

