### Data collection

2.7.

We will administer surveys at baseline (prior to randomization), 3 months (prior to re-randomization), and 6 months. To minimize participant burden, follow-up assessments will be conducted by phone and participants will be sent the survey by email ahead of the call. Participants will be called up to 5 times at each time point at which measures are collected. Because all participants will be patients at AHWFB, we will also be able to follow-up with participants at their prenatal care visits if we are unable to reach them by phone. We will provide graduated compensation ($20 at baseline, $40 at 3 months, and $60 at 6 months) to reduce the risk of loss to follow up. Surveys will be collected using REDCap, a secure application for building and managing surveys and databases. Participants will complete the surveys on a tablet or computer at their baseline visit and over the phone at follow-up visits. We will also extract data from the EHR regarding participants’ demographics, clinical characteristics, and outcomes (Table 2). Study staff will place CGM devices on participants at the initial in-person baseline visit and mail them to participants at 6 months to self-place. Participants will receive video and written instructions on the CGMs. After 14 days, staff will instruct participants on device removal. The device is painless to apply, requires no interaction after placement, and should not hinder activities of daily life. The device results will be blinded to avoid participants changing behavior based on the readings.

As quantitative measures may not fully capture the complex behavioral and contextual processes, an embedded qualitative approach has been included to produce a richer understanding of the interventions’ effects. We will conduct semi-structured interviews (in English or Spanish) with 2 groups of participants at the end of their 6-month follow-up: participants who 1) had a ≥ 2-point decrease in FI (*n* = 15) and 2) did not have ≥2-point decrease in FI (n = 15). The sample size of 30 participants should be adequate to reach thematic saturation, but we will have flexibility to expand if warranted. Interviews will help generate hypotheses about potential mechanisms of intervention effects, inform future modifications, assess acceptability of the interventions, and help further develop an effective adaptive intervention. Those who complete an interview will receive an additional $25.

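### For re-randomized participants, the second glucose-monitor window nominally begins when Stage 2 food ends, so it records glucose after produce or meals have stopped

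*Protocol article*

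**What the plan says.** All references are to the protocol article.

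- **Status and timing of the monitor.** Overall study design: "As an exploratory aim, participants will wear a continuous glucose monitor (CGM) at 2 time points", namely "baseline (first 2 weeks) and at 6-month follow up". Table 2 lists 14-day glucose monitoring at months 0 and 6.
- **How the second sensor is supplied.** Data collection: staff place the first device in person, then "mail them to participants at 6 months to self-place". Removal is after 14 days.
- **When Stage 2 food runs.** The Abstract and the section on Stage 2 interventions give 3 months of weekly supply after the 3-month re-randomization. For the meals arm the words are "delivered to their home weekly for 3 months", and the produce arm has the same length. Overall study design gives a total intervention period of up to 6 months.
- **Gestational age at entry.** Recruitment and consent: "The nurse intake visit is ideally performed at 8 weeks gestation", and the initial prenatal visit follows 1 to 2 weeks later. Participants "will be randomized at their initial prenatal visit to one of two first-stage interventions for 3 months". Table 1 admits anyone in the first trimester at that visit.

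**The concern.** A glucose sensor records forward from the moment it is placed. If it is placed when the food supply stops, it cannot show glucose while participants were receiving produce or meals. The month-6 food-security survey does not share this problem, because its 30-day reference period looks back into the last month of deliveries. The same label, month 6, therefore means the end of treatment for the survey and the period after treatment for the sensor.

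What is at stake is how the exploratory glucose data in the re-randomized group can be read. The pilot is also meant to refine the protocol for a definitive trial, so an unhelpful measurement window could be carried forward. A second, smaller issue is that the window falls close to term, so its completeness and meaning depend on when each participant delivers, and preterm delivery is itself a study outcome.

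**Working it through.** The document gives no sample size, power or precision figure for the glucose measure, so there is none to reproduce. The check is calendar arithmetic, with 6 months = 26.1 weeks and 3 months = 13.0 weeks.

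**1. Overlap of the second window with food delivery (weeks since first randomization)**

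- Stage 2 deliveries: 13.0 to 13.0 + 13.0 = about 26.
- Second sensor: 26.1 to 26.1 + 2 = 28.1.
- Nominal overlap: 0 weeks.
- Survey look-back at month 6, for comparison: 30 days = 4.3 weeks, so 26.1 - 4.3 = 21.8 to 26.1, wholly inside the delivery period.

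**2. Effect of delays**

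Let L be the delay in starting deliveries and M the delay from month 6 to sensor placement, both in weeks. If deliveries still run a full 3 months from a late start, overlap = min(2, max(0, L - M)).

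| L | M | Overlap (weeks) |
|---|---|---|
| 0 | 0 | 0 |
| 1 | 0 | 1 |
| 1 | 1 | 0 |
| 2 | 0 | 2 |

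Delay in starting Stage 2 creates overlap, and mailing delay takes it away. If deliveries are instead cut off at month 6, in line with the 6-month cap on the intervention period, L creates no overlap.

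**3. Gestational age during the second window**

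Start = gestational age at entry + 26.1 weeks; end = start + 2 weeks. Entry on the stated schedule is 8 + 1 = 9 to 8 + 2 = 10 weeks. The last row is the eligibility ceiling. The document gives no week for the end of the first trimester, so 13 weeks 6 days is an assumption.

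| Entry (weeks) | Sensor on | Sensor off |
|---|---|---|
| 9 | 35.1 | 37.1 |
| 10 | 36.1 | 38.1 |
| 12 | 38.1 | 40.1 |
| 13w6d | 39.9 | 41.9 |

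If 6 months is read as 24 weeks, the sensor goes on at 33.0 to 37.9 weeks across the same range of entry.

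Table 2 defines preterm delivery as before 37 weeks. Even with entry at 9 weeks the window ends at 37.1 weeks, so any preterm delivery falls before or during wear.

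**4. Share delivered by the start and end of wear (assumption)**

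The document gives no distribution of delivery timing. Taking it as normal with mean 38.5 to 39.5 weeks and SD 1.5 to 2.5 weeks:

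| Entry (weeks) | Delivered before sensor on | Delivered before sensor off |
|---|---|---|
| 9-10 | about 0-17% | about 6-44% |
| 12 | about 18-44% | about 60-86% |
| 13w6d | about 57-84% | about 84-99% |

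**5. If wear ended at month 6**

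Wear would run from 26.1 - 2 = 24.1 to 26.1 weeks after randomization, inside the delivery period. For entry at 9 to 10 weeks this is 33.1-34.1 to 35.1-36.1 weeks of gestation. Since the moved window ends where the present one starts, the share delivered before its end is the middle column above: about 0-17% instead of 6-44% for entry at 9 to 10 weeks.

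**The case against.** Several points on the other side have force.

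- **Zero overlap is the nominal calendar.** Re-randomization waits for the 3-month survey, which may take up to five calls or a prenatal visit, and deliveries must then be arranged. Some deliveries may run past month 6, and some meals are frozen and could be eaten later. This stands as a limit on the claim. But such overlap would be accidental and would vary between participants, so it does not rescue the schedule.
- **No passage names a glucose comparison of produce with meals.** This is true. The analysis section compares outcomes in general across the four embedded interventions and expects no significant differences. The point therefore concerns any such exploratory comparison, not a stated hypothesis.
- **Responders receive no Stage 2 food.** The sample-size section assumes a 40% response rate, so the point concerns about 60% of the 60 participants, or 36 before attrition. The Stage 1 comparison is not undermined by deliveries stopping.
- **Visit windows and shipping details may sit in the full protocol**, which is not shown. That could soften the problem, but the article states the mailing time plainly.

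Three stronger readings are tempting, and the document does not support them.

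- *The first window is invalid as well.* Since "After baseline data are obtained, participants will be randomized", and both happen at the initial prenatal visit, the first 14 days of wear do follow randomization. But the window is openly described as the first 2 weeks, no study food is supplied then, and no passage uses the readings as a pre-randomization covariate. Relabelling would change no planned analysis.
- *Many participants will already have delivered when the sensor goes on.* On the stated 9-to-10-week schedule the sensor goes on at about 35 to 36 weeks, and under the assumed distributions at most about 17% have delivered. Large shares arise only for late first-trimester entry, which is the eligibility ceiling and not the described routine.
- *The data will be missing after delivery.* No rule withholds the sensor from those who have delivered, and everyone is followed past delivery. Truncation is possible, but so is a mixture of pregnancy and postpartum readings.

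**Conclusion.** The point holds for the second window only, and for re-randomized participants. On the article's own timeline the sensor is worn at about weeks 26 to 28 and food is delivered at about weeks 13 to 26, so nominal overlap is zero weeks. Any glucose contrast between produce and meals would describe the period after both had ended. This rests on Stage 2 starting promptly at month 3 and on mailing at month 6 as written.

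The window is also near term: about 35-36 to 37-38 weeks for entry at 9 to 10 weeks, and later for late first-trimester entry. Preterm delivery would shorten it or mix in postpartum readings. How often delivery of any kind intervenes depends on an assumed distribution that the document does not supply.

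The consequence is minor. The measure is exploratory, and recruitment, retention, re-randomization and the food-insecurity score are untouched. This is a cheap improvement to what the monitor can show, not a defect in the trial's main aims.

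**What to change.** Send the second sensor about two weeks earlier, with an allowance for mailing time, so that the 14 days end at month 6. For re-randomized participants an alternative is to end wear with the last scheduled delivery. Ending at month 6 has the advantage of a common timing for responders and non-responders, and it stays inside the delivery period even if Stage 2 starts some weeks late.

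The cost is an earlier mailing of the same device and a small change to the protocol text and Table 2. Wear would precede the month-6 survey instead of following it. Recruitment began in June 2025 and is expected to finish at the end of 2026, so some participants may already have worn the second sensor on the present schedule. Recording the wear dates against the last food delivery and the date of delivery would let the two timings be told apart.

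The change reduces the delivery-timing problem without removing it. With entry at 13 weeks 6 days, wear would still run to about 39.9 weeks.
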